**Figure 1 f1:**
[figure not shown]
Timeline of study participation. During days −7 to −1, participants maintain a regular sleep schedule. Day 0 (lab session) is indicative of a participant with a habitual wake time of 8 am. Lab session timing depends on participant sleep schedule. All sessions are a maximum of 6 h long. For the night following the lab session, participants follow the regular sleep schedule. For the remaining four nights of sleep, participants sleep ad libitum. During days 1–5, participants complete a daily mind wandering task (sustained attention task), fill out a diary for intrusive memories, and repeat the recognition task on the final day.

Phase 2 is the lab session (day 0). Participants wake up 2 h prior to their habitual wake time. This is to ensure sufficient sleep during the nap and to mildly sleep-deprive the wake group. After reporting to the lab in the morning participants are set-up with polysomnography. Following this, they view an analog trauma film in a dark sound attenuated room. Participants are then randomly assigned to one of the two groups: an experimental (nap) group and a controlled (wake) group, for a 2-h period. During this time, those in the wake group can engage in specific activities provided by the researchers including coloring and puzzles. They are unable to use social media, watch videos, view photos, read, or engage in university study/other work during this time. At the end of this experimental period, polysomnography equipment is removed and there is a 30-min delay period for both groups, to allow for the effects of sleep inertia to subside for the nap group. Participants then complete a recognition memory task for images from the trauma film and a sustained attention task to measure mind wandering (hereinafter referred to as “mind wandering task”) in the same sound attenuated room. Following this, participants are provided with instructions for completing an intrusive memory diary.

Phase 3 includes the remaining 5 days of the experiment. Over the next five nights, we will continue to monitor participant sleep with diaries and actigraphy. Participants complete daily intrusive memory diaries, starting as soon as they leave the lab, with six entries at minimum. During each day, they complete the same mind-wandering task completed during the lab session. The recognition task is repeated on day 5. Following study completion, participants attend a debrief meeting.

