##### Post-lab session sleep monitoring (days 0–5)

Sleep (at-home) for five nights following viewing the trauma film is measured via actigraphy and sleep diaries. The night following the lab session, participants are required to follow their assigned sleep schedule. Across the remaining four nights participants are not required to follow a regular sleep schedule on these nights. Primary sleep variables measured during this time will be objective total sleep time and sleep efficiency. Secondary variables will include sleep diary-based variables (subjective total sleep time and sleep efficiency).

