## Analytic strategies

All analyses will be conducted in R.

Aim 1: The effect of a daytime nap (vs wake) on total intrusive memory frequency will be analyzed with a generalized linear mixed-effects model. Sex and day will be included as covariates. A random intercept for participant will be included to account for repeated measures across days.

Aim 2: The effect of sleep-related memory consolidation on intrusive memory frequency will be analyzed with regression and mediation analysis. Specifically, Hypothesis 2a (a nap will lead to greater recognition memory for the trauma film) will be examined with multiple regression, whereby recognition memory immediately after the nap/wake will be predicted by Condition. For Hypothesis 2b (recognition memory will mediate the relationship between sleep and intrusive memories), we will utilize mediation analysis, with Condition as the explanatory variable, recognition memory immediately after the nap/wake as the mediator, and total number of reported intrusive memories as the dependent variable. A Monte Carlo power analysis was conducted for the mediation model. A sample size of *n* = 114 has limited power to detect the indirect effect. Nonetheless, given the strong theoretical rationale for the mediation analysis and the value for future research in determining effect sizes, we will conduct the analysis and consider Hypothesis 2b as a secondary analysis. We will report effect sizes and confidence intervals of each path. We will also conduct parallel exploratory analyses for both Hypotheses 2a and 2b, utilizing recognition memory on day 5, rather than memory immediately following the nap/wake. This will explore the role of longer-delay memory consolidation on intrusive memory. Note, Hypothesis 2b may appear dependent on the success of Aim 1.

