Aim 3: The effect of overnight sleep on next-day mind wandering and intrusive memory frequency will be analyzed with mixed models. In two separate analyses, Hypothesis 3a (reduced sleep will be associated with increased mind wandering and increased intrusive memories the next day) will use sleep (total sleep time, sleep efficiency) each night to predict frequency of mind wandering and number of intrusions the next day. Hypothesis 3b (mind wandering will mediate the relationship between sleep and intrusive memories the next day) will be tested with two mediation analyses. Sleep duration each night will serve as the explanatory variable, mind wandering the next day will serve as the mediator, and number of intrusions the next day will be the dependent variable. Hypothesis 3b is also considered a secondary analysis. We were unable to perform a power analysis for this mediation as there are no previous studies examining the effect of sleep on both spontaneous cognition and intrusive memories, and thus, no basis for estimating effects sizes. If this mediation model is significant, as an exploratory analysis, we will also run a moderated mediation to explore if Condition moderates the relationship between mind wandering and intrusive memories, in the context of the mediation analysis. A separate set of models with sleep efficiency as the explanatory variable will also be run as an exploratory analysis. If the structure of the data (eg, excessive zero counts in the intrusive memory data) does not allow for mediation, alternative analytical strategies will be developed to address the same aim for Hypotheses 2b and 3b.

For Hypothesis 1 and Hypothesis 3a, we will run additional secondary analyses to examine the influence of trait mind wandering, mindful attention, frequency of intrusive thoughts, perseverative thinking and maladaptive daydreaming on the relationship between sleep and intrusive memories. Each trait measure will be examined in a separate model, where the given trait measure is added to the primary model for Hypotheses 1 or 3a. We will examine the main effect of the trait measure, as well as the interaction between the trait measures and the primary effect of interest for each model. These analyses will allow us to determine if trait factors theoretically related to the vulnerability to intrusive memory or mind wandering influence the sleep effect.

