### Exploratory analyses

Several exploratory analyses will also be conducted in this study. Specific examples include: (1) The influence of sex on intrusive memory frequency will be examined, as some evidence suggests females experience more frequent intrusive memories following actual [66] and analog [67] trauma exposure during certain phases of the menstrual cycle. (2) In the day-to-day analysis, we will analyze the effect of accumulation of sleep over multiple days on mind wandering and intrusive memory frequency. (3) We will further expand the temporal aspects of the model in Hypothesis 3 to include sleep the night before the lab session (night −1, day 0), to examine sleep’s effect on mind wandering and intrusive memories over a 6-day period. (4) The effect of the nap on mind wandering and intrusive memories on day 0 will also be examined. (5) A further outcome of the mind wandering task will be how many reports of mind wandering are related to the film.

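### The Aim 3 intrusion models name nightly sleep but not day, although the design ties sleep to day and Aim 1 adjusts the same daily counts for it

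*Protocol article*

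**What the plan says.** Under Analytic strategies, Aim 1 models daily intrusion counts with a participant random intercept, and "Sex and day will be included as covariates". For Aim 3, "The effect of overnight sleep on next-day mind wandering and intrusive memory frequency will be analyzed with mixed models"; Hypothesis 3a "will use sleep (total sleep time, sleep efficiency) each night to predict frequency of mind wandering and number of intrusions the next day". Hypothesis 3b takes sleep duration as the explanatory variable, mind wandering as the mediator and next-day intrusions as the outcome. No covariate is listed for either. Condition appears in Aim 3 only in an exploratory step, run if the mediation is significant, to "explore if Condition moderates the relationship between mind wandering and intrusive memories".

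The sleep regime changes by day. Post-lab session sleep monitoring states: "The night following the lab session, participants are required to follow their assigned sleep schedule". The Figure 1 legend adds: "For the remaining four nights of sleep, participants sleep ad libitum". Under Sleep schedule adherence and Data exclusion, a participant who breaks the schedule on that first night is excluded.

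Among the Exploratory analyses: "We will further expand the temporal aspects of the model in Hypothesis 3 to include sleep the night before the lab session", paired with day 0. That night is cut short for everyone. Study design says of the lab day: "Participants wake up 2 h prior to their habitual wake time".

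The Introduction notes that in many people intrusive memories fade with time after trauma. The article gives no daily intrusion rate and no expected difference in sleep between scheduled and free nights.

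**The concern.** Day is a confounder of the sleep-intrusion association if it is related to both. The protocol itself creates the link with sleep, through one controlled night followed by four free ones. A decline in intrusions after the film would supply the other link, and adjusting for day in Aim 1 makes sense only if the counts may change over days. A model with nightly sleep alone then attributes part of the calendar trend to sleep.

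Aim 3 is where the executive-control mechanism, one of the two that the project sets out to examine, is tested. Hypothesis 3b is labelled secondary; Hypothesis 3a is not. A positive or negative answer on sleep and intrusions could therefore reflect the study calendar and not sleep.

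**Working it through.** The plan states no figure for Aim 3, so there is none to reproduce.

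**Inputs from the protocol article.** 114 participants, five days after the lab session, first night scheduled and four free, two-sided 0.05.

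**Assumed, because the documents are silent.** A day-1 mean of 1 intrusion; a constant daily decline of 0% to 50%; free nights longer than the scheduled night by δ hours, with δ from -0.5 to +1.0; within-person SD of sleep σ = 1.0 h and between-person SD 0.7 h. The true sleep effect is zero.

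**Step 1: expected spurious slope by hand.** Let μ₁ be the day-1 mean and μ̄ the mean over five days. Four of five nights are free, so the shift adds 0.8 × 0.2 × δ² = 0.16δ² to the variance of sleep, and its covariance with the daily mean is -0.2δ(μ₁ - μ̄). The log rate ratio per hour of sleep, without day in the model, is approximately

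β ≈ -0.2δ(μ₁ - μ̄) / [μ̄(σ² + 0.16δ²)].

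For a 35% decline the daily means are 1, 0.65, 0.4225, 0.2746 and 0.1785, so μ̄ = 2.5256/5 = 0.505. With δ = 0.5, β ≈ -0.2 × 0.5 × 0.495 / (0.505 × 1.04) = -0.094, a rate ratio of 0.91. The formula shows the structure. The bias is zero if there is no decline (μ₁ = μ̄) or no shift (δ = 0), and its sign follows δ.

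**Step 2: simulation.** 400 trials per scenario, Poisson mixed model with gamma random intercept, likelihood-ratio test of sleep. Monte Carlo standard error at 5% is √(0.05 × 0.95/400) = 1.1 points.

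| Daily decline | δ (h) | Rate ratio per hour, sleep only | Significant, sleep only | Significant, day added |
|---|---|---|---|---|
| 0% | +0.5 | 1.00 | 7.5% | 7.2% |
| 20% | 0 | 1.01 | 5.5% | 4.0% |
| 20% | +0.25 | 0.97 | 8.0% | 3.3% |
| 20% | +0.5 | 0.96 | 15.5% | 4.5% |
| 35% | +0.5 | 0.91 | 37.5% | 4.3% |
| 50% | +0.5 | 0.86 | 63.2% | 3.3% |
| 35% | +1.0 | 0.84 | 85.0% | 4.3% |
| 35% | -0.5 | 1.10 | 38.0%, all against the hypothesis | 5.0% |

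The simulated rate ratio of 0.91 at 35% and +0.5 h agrees with Step 1.

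**Step 3: a second set of assumptions.** 300 trials per setting, Poisson GEE in place of the mixed model, daily means falling from 1.5 to 0.4, nightly SD 0.9 h. With the first night 0.25, 0.5 or 0.75 h shorter than later nights, false positives were 11%, 27% and 43%. With it 0.5 h longer, they were 25%, in the opposite direction. With day in the model they were 5% to 9%. A repeat of the 0.5 h setting gave 21% without day and 7% with it. Under a mild decline, from 1.0 to 0.7 over the period, the rate without day was only 7%.

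**Step 4: do Condition or centring account for it?** Within-person centring without day left the rate at 16% (20% decline, +0.5 h), 46% (35%, +0.5 h) and 88% (35%, +1.0 h), because the calendar trend lies within person. Letting the nap lower both intrusions (rate ratio 0.65) and first-night sleep (by 0.5 h), with no decline and no regime shift, left the rate at 5% with Condition omitted.

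**The case against.** The strongest reply is that the article is silent on Aim 3 covariates and does not exclude them. It lists no random effect for Aim 3 either, so the description is abbreviated, and the cited preregistration, not shown here, may name day. This stands as a caution: a reader should not infer that the authors decided to leave day out. What remains is the contrast within one section. Covariates are given for Aim 1 and not for Aim 3 on the same counts, and the trait analyses then build on the primary Hypothesis 3a model as if it had been specified.

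The second reply is that size and direction are assumed. This also stands. The remark that intrusions fade concerns real trauma. The assigned schedule is set from each participant's habitual sleep, so the shift on free nights may be small. Free nights may be longer because oversleeping is no longer barred, or shorter if the first night absorbs recovery from the early waking. A reader might infer that the omission favours the hypothesis; the documents do not settle that.

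Three further inferences are not supported:

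- That omitting Condition or centring produces this artefact. Condition is randomised, and Step 4 shows neither is the cause.
- That the sleep-to-mind-wandering path is biased too. Nothing in the article says mind wandering changes over days, and it was not simulated.
- That the 6-day extension is almost bound to mislead. Simulated false-positive rates of 97% and 91% without day rest on a high day-0 count. Diary recording on day 0 starts only when participants leave the lab, and halving the assumed day-0 mean of 1.8 gave 8.5%. The analysis is also exploratory.

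**Conclusion.** The concern holds for the intrusion outcome in Hypotheses 3a and 3b. Followed as written, the models leave out a variable that the design ties to sleep and that Aim 1 adjusts for on the same data. The bias needs both an appreciable decline in intrusions and a difference in sleep between scheduled and free nights. With an assumed 0.5 h difference and daily declines of 20% to 50%, false positives are roughly 15% to 63%. With either ingredient absent they are near nominal, and with day in the model about 3% to 9%. The pattern is general; the percentages depend on the assumed decline, shift and SDs. The exploratory extension has the same structure, with a 2 h cut for everyone before the day nearest the film, but its size is uncertain.

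Between- versus within-person sleep is a separate matter. Hypothesis 3a asks about the previous night, whereas raw nightly sleep also carries stable differences between people.

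**What to change.** State that day enters the Hypothesis 3a and 3b models and the exploratory 6-day extension as a categorical fixed effect, with sex as in Aim 1. Categorical coding suits the step from one scheduled night to four free ones better than a straight line. If the preregistration already says this, the article should say so.

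As a separate change, split nightly sleep into each person's mean and the nightly deviation from it, and test Hypothesis 3a on the deviation. This does not replace day. Condition may be added for precision. A waking-hours offset is not needed: it would change the outcome from intrusions per day to intrusions per waking hour.

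The cost is four degrees of freedom for day over five days (five over six days), and one each for sex, the person mean and, if used, Condition. All variables are already being collected, and final analysis begins only after data collection ends.

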## Introduction

Intrusive memories are spontaneous, involuntary intrusions of memories, typically sensory experiences (eg, sights, sounds, smells), into conscious awareness [1–3]. While in many individuals intrusive memories tend to dissipate over time following trauma, for those with posttraumatic stress disorder (PTSD), this symptom can remain distressing and persistent for many years [1]. Sleep disturbance, another common symptom following trauma, is conceptualized as both a symptom of PTSD and a comorbid disorder [4]. Evidence suggests sleep disturbance prior to [5–7] and early after [7–9] trauma predicts the development of PTSD. Sleep disturbance is also related to intrusive memories specifically. For example, sleep disturbance is associated with more frequent intrusive memories in the week after experiencing trauma [10, 11]. Even many years after trauma exposure, disturbed sleep the previous night is still associated with more intrusive memories the following day [12].

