A second potential mechanism explaining the role of sleep in intrusive memories relates to sleep disturbances increasing disruptive spontaneous cognition (eg, mind wandering), which in turn accounts for the involuntary intrusion of trauma memories into awareness [19, 32]. Mind wandering occurs when, instead of being focused on task relevant demands, attention is captured by internal stream of thought [33]. Notably, increased mind wandering has been observed following both self-reported poor sleep [34] and experimental sleep deprivation [19, 35] and may occur via sleep’s effect on reduced executive control [32]. Therefore, reduced top-down executive control over traumatic autobiographical memories would be expected to increase the likelihood of the memories becoming intrusive. This process may be exacerbated by sleep deprivation, due to the resultant negative impact on executive control [19, 36]. As people frequently experience sleep difficulty following trauma [37], this explanation may represent an important mechanism for the early maintenance of intrusive memories.

In summary, sleep disturbance plays a role in the development of intrusive memories following trauma exposure [19–22]. The critical gap in the literature is understanding the mechanism(s) whereby sleep exerts this influence [36]. The current project will address this through an experimental study in healthy adults. We are utilizing a nap vs wake design, rather than overnight sleep vs sleep deprivation design, as in addition to reducing the frequency of intrusive memories, naps are found to improve memory for a range of emotional [23, 38] and neutral stimuli [39]. Utilizing a nap/wake paradigm also ensures intrusion frequency is due to sleep rather than the effect of total sleep deprivation (eg, if using an overnight wake period) or potential circadian confounds of comparing a day of wake to a night of sleep immediately following exposure to the trauma film. The current study will be the first to examine memory consolidation as a mechanism linking sleep to intrusive memories using a nap versus wake design, as well as the first to examine mind wandering as a mechanism linking sleep to intrusive memories, using any type of design. Additionally, we will examine natural variation in sleep across multiple nights following analog trauma exposure to examine the relationships between sleep the night before and both mind wandering and intrusive memories the following day.

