##### Intrusive memory diary (days 0–5)

Following completion of the cognitive tasks, participants are provided with a definition of intrusive memories and instructions for completing the intrusive memory diary. The diary is completed online, accessible via smartphone, or computer. There are a total of seven questions, including the date and time of the intrusion, the type (eg, image, sound, thought(s)), content of the intrusive memory, whether the intrusive memory was triggered, and level of distress and vividness rating. This diary was based on an online diary used in a trauma film study by Zeng et al. (2021) [13].

An email with the intrusive memory diary link is sent to participants as soon as they leave the lab on day 0. Participants are instructed to complete the diary as soon as possible following the experience of an intrusive memory, completing this as many times as needed. A reminder with the intrusive memory diary link is also sent via text message to participants each evening (between 1 and 3 h prior to scheduled bedtime, based on the previous week), beginning the first evening following the lab session. Participants are instructed to fill out the diary at the end of the evening after receiving the text reminder, even if they have not experienced an intrusive memory. Participants can select an N/A option to each of the diary questions, reducing demand characteristics to report an intrusive memory even if one did not occur. Thus, participants complete the diary a minimum of six times. The primary outcomes from the intrusive memory diary are the total number of intrusive memories following the lab session and number of intrusive memories each day. Secondary outcomes include examining level of distress ratings (1 = not at all distressed, 9 = extremely distressed) when intrusive memories occur.

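### Aim 3: the model of last night's sleep on next-day intrusions has no term for the previous day's intrusions, so a negative association can arise without any effect of sleep

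*Protocol article*

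**What the plan says.** Under Analytic strategies, Aim 3, the plan states: "The effect of overnight sleep on next-day mind wandering and intrusive memory frequency will be analyzed with mixed models". In two separate analyses Hypothesis 3a "will use sleep (total sleep time, sleep efficiency) each night to predict frequency of mind wandering and number of intrusions the next day". For Hypothesis 3b, "Sleep duration each night will serve as the explanatory variable, mind wandering the next day will serve as the mediator", with next-day intrusions as the outcome. The plan adds: "Hypothesis 3b is also considered a secondary analysis".

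The named extensions are the trait questionnaires, Condition as a moderator, and sleep efficiency as an alternative explanatory variable. Exploratory analyses adds sleep accumulated over several days and the night before the lab session. Two of these reach back in time, but for sleep. None enters the previous day's intrusions, and none asks whether intrusions predict that night's sleep.

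For Aim 1 the model terms are given: "Sex and day will be included as covariates", with a random intercept for participant. No such list is given for Aim 3.

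The Figure 1 legend and Post-lab session sleep monitoring fix the sleep schedule for the first night after the film and leave the other four nights free. The Introduction describes disturbed sleep as a consequence of trauma: "Sleep disturbance, another common symptom following trauma, is conceptualized as both a symptom of PTSD and a comorbid disorder", and again "As people frequently experience sleep difficulty following trauma". On the diary: "An email with the intrusive memory diary link is sent to participants as soon as they leave the lab on day 0". The daily count is one of its primary outcomes.

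**The concern.** Only the nap is randomised. In Aim 3 the exposure is each person's own sleep, which may respond to the day just lived. If a day with many intrusions costs sleep that night, and intrusive days come in runs, then yesterday's intrusions are a common cause of a short night and of today's intrusions. A model containing sleep but not yesterday's intrusions counts that path as a sleep effect. A participant random intercept absorbs stable differences between people, not carry-over from one day to the next.

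Aim 3 is the plan's test of the executive-control account, and its analysis is introduced as an effect of overnight sleep. A negative slope for intrusions could be read as support for that account when it reflects the opposite direction.

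**Working it through.** The plan gives no figure for Aim 3 to reproduce. Its sample-size calculation concerns Hypothesis 1, and it says no power analysis was possible for Hypothesis 3b. The check is therefore a simulation with a true sleep effect of zero.

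**From the plan:** 114 participants (57 per condition), five nights each followed by a daily count, and a diary opening on day 0, so a preceding count exists for every night.

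**Assumed, not in the plan:**
- A day-0 base of about 2 intrusions, falling by about 22% per day (e^−0.25 = 0.78).
- Random-intercept SD 0.6–0.8; sleep SD 0.6 h between and 0.9 h within persons.
- Reverse path: sleep = usual sleep − γ × log(1 + previous day's count) + noise. One intrusion then costs γ × log 2 = γ × 0.693 h, which is 4, 10 or 21 minutes at γ = 0.1, 0.25 or 0.5 h.
- Carry-over in one of two forms: φ × log(1 + previous count) added to the log-rate (300 runs per cell), or a latent AR(1) day effect with correlation ρ (200 runs per cell).

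**Fitted model:** Poisson mixed model with participant random intercept, Wald test at 1.96. Entries are the percentage of runs significant in the hypothesised direction (nominal 2.5%). The last two columns also contain day and Condition.

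| Carry-over | γ (h) | Sleep only | + day, Condition | + previous day's count | Within-person sleep, no lag |
|---|---|---|---|---|---|
| φ = 0.4 | 0 | 9 | 4 | 3 | 2 |
| φ = 0.4 | 0.1 | 14 | 8 | 3 | 2 |
| φ = 0.4 | 0.25 | 24 | 12 | 3 | 2 |
| φ = 0.4 | 0.5 | 45 | 31 | 3 | 3 |
| ρ = 0.5 | 0 | 6 | 6 | 6 | 6 |
| ρ = 0.5 | 0.25 | 17 | 7 | 6 | 4 |
| ρ = 0.5 | 0.5 | 33 | 14 | 6 | 3 |
| ρ = 0.8 | 0.25 | 21 | 12 | 5 | 3 |
| ρ = 0.8 | 0.5 | 41 | 18 | 5 | 3 |
| φ = 0.2 | 0.1 | 9 | 4 | 3 | 2 |
| φ = 0.2 | 0.25 | 17 | 5 | 3 | 1 |

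Monte Carlo error is about 1–3 points. For example, √(0.45 × 0.55 / 300) = 2.9 points and √(0.07 × 0.93 / 200) = 1.8 points.

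The rows with γ = 0 show that serial correlation alone lifts the error rate somewhat (9% and 6% with sleep only). The share due to feedback is the rise above those rows.

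**Size of the spurious slope** in the φ = 0.4 and AR(1) rows with γ > 0: −0.013 to −0.074 log-rate per hour with sleep only, that is 1.3% to 7.1% fewer intrusions per hour of sleep (e^−0.013 = 0.987, e^−0.074 = 0.929). With day and Condition it is −0.011 to −0.051, or 1.1% to 5.0%.

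**A second simulation** used a Poisson GEE with day as a factor and sleep centred on the run-in mean, losing 10, 15 or 30 minutes per intrusion, with autocorrelation 0.3–0.6. Two-sided rejection was 13–19%, 15–21% and 37–58%, against 6–8% without feedback. With log(1 + previous count) added it was 6–10%. Run-in centring alone therefore does not remove the problem.

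**Hypothesis 3b.** With mind wandering unrelated to intrusions, the joint test of the two mediation paths was positive in 0–1% of runs. With an extra assumption that same-day intrusions raise mind wandering, it was 5–7% with sleep only and 4% with the lag.

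**The case against.** The strongest reply is that this is an article. It gives no covariates, random effects or centring for Aim 3, repeated days need at least a participant effect, and a preregistration is cited but not shown. A reader might infer that the full plan certainly omits a lag; the article does not establish that. What stands is that it names the predictors and lists its extensions, and neither list contains this term.

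Second, the feedback is assumed. The Introduction speaks of trauma and PTSD, whereas these are healthy adults, and the Discussion concedes that intrusion-related distress is elicited inconsistently in this paradigm. On the first night, when counts are likely highest, sleep is scheduled. All of this argues for the lower end of the range.

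Third, splitting sleep into within-person and between-person parts gave 2–4% in the feedback rows with moderate carry-over, without any lag. This stands too, but the article does not commit to it. It can also bias the slope the other way: +0.018 per hour at ρ = 0.5, γ = 0.5, and +0.029 at γ = 0.25 with no carry-over. That would hide a real benefit of sleep rather than create a false one.

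Fourth, a lagged outcome with a random intercept has its own initial-condition bias. Day 0 covers only the hours after the lab session, and conditioning on yesterday's count changes what the slope means. These are good reasons not to rest the conclusion on the lagged model alone.

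A reader might also infer that the mediation result in Hypothesis 3b would be spurious. The 0–1% figure does not support that, and the mind-wandering half of 3a likewise needs a further link from intrusions to mind wandering. Hypothesis 3a is worded as an association, 3b is secondary, and the randomised Hypothesis 1 is untouched.

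**Conclusion.** The point holds for the sleep-to-intrusions analysis in Hypothesis 3a and for the total sleep-to-intrusions path in 3b. With no sleep effect, moderate carry-over and γ of 0.1–0.5 h, false support arises in 14–45% of trials with sleep only and 7–31% with day and Condition, against a nominal 2.5%. With weak carry-over and those two covariates it is 4–5%, which is little to worry about.

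Adding the previous day's count brought the rate to 3–6%, the level seen without feedback. In the second simulation it removed most of the excess. Some can remain if the form of the lag does not match the way intrusions cost sleep.

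The direction of the bias is firm if both paths exist. Its size depends on minutes lost and day-to-day correlation, neither of which the plan gives, and on modelling choices the article leaves open. The documents do not show that a positive Hypothesis 3a result would be an artefact, only that the stated model could not tell the two explanations apart.

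**What to change.** For the Hypothesis 3a intrusion model:

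- Include day and Condition, and separate within-person from between-person sleep, or centre sleep on the pre-film run-in week. The first removes most false support but can lean the other way. The second avoids that lean but still needs the lag.
- Prespecify a companion model that adds the previous day's intrusion count, for example log(1 + count), with day 0 treated as a part-day. Report it beside the stated model.
- Report the reverse model, with today's intrusions predicting tonight's sleep.
- State that the association will be interpreted as an effect of sleep only if it holds with the lag, and apply the same reading to the total path in Hypothesis 3b.

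The cost is some analysis wording and a few lines of code, with no new data. Data collection is estimated to run to July 2026 and final analysis follows it, so this can be fixed beforehand. The price is one extra parameter, slightly wider intervals and some initial-condition bias in the lagged model, which is why both models should be shown.
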